## Methods/design

### Study design

We propose a multiple baseline interrupted time series (ITS) design (using month as a time unit) which compares our stated outcomes over 12 months before and 12 months after the implementation (over a 1-month transition period, with possible inter-site variability based on site size) of the theory-based educational intervention on recognition of agonal breathing. The ITS design is a robust quasi-experimental design which is ideal for our study because: 1) Withholding this potentially life-saving intervention from control groups could possibly be considered unethical by some review boards; 2) Most sites would only participate if ultimately given an opportunity to implement the intervention; and 3) It will account for heterogeneity across sites in their underlying baseline trends and changes in response to the intervention. In addition, this design will give us the ability to explore the effects of our intervention while taking into account possible seasonal variations and secular trends.

Each site will implement the educational program on agonal breathing at their earliest convenience, and enter into a 12-month evaluation period (12 months/time periods after the implementation of the educational program). The evaluation period for all sites could possibly be spread over 18 months given their respective training completion. This will leave us with 6–12 months to complete data collection and analyses.

Data for the 12-month control period preceding the implementation of the educational program (12 months/time periods) will be obtained retrospectively once a site’s evaluation period is determined. Ambulance Communication Centres are already required to keep their telecommunication recordings for at least 5 years, and CanROC will have already prospectively collected all the other required outcome measures throughout.

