**Information about the significance of agonal breathing:**This first module will consist of a 20-min video detailing information about the early clinical signs of cardiac arrest, including agonal breathing. The original 30-min video used in our pilot study was reviewed in collaboration with a committee of telecommunication leaders from participating sites. Its content was shortened by 10 min, references to existing protocols were updated, and a visual representation of agonal breathing was added. Telecommunicators employed by the participating sites will all review this short educational video individually. Site implementation will commence once all regulatory requirements are met for that site and is expected to be staggered over a 6-month period for all sites. Completion of staff training at each site is expected to be completed within 1 month.**Modeling/demonstration of desired behavioural skills:**The video will include a number of real interventions involving the description of agonal breathing by 9–1-1 callers. These interactions are judged to be optimal examples to emulate.**Rehearsal of desired skills:**A second, shorter module will be updated with new cases of agonal breathing and interactions with 9–1-1 callers and completed once in the middle of the intervention period.**Monitoring/reinforcement and feedback:**Each time an ambulance telecommunicator is involved with a cardiac arrest call, they will be provided with a report card which will include various time intervals measured during the review of the recording (time to cardiac arrest recognition, time to initiation of chest compressions), whether or not the victim was indeed in cardiac arrest upon EMS arrival at the scene, and an opportunity to review their performance with their supervisor. We understand that not all sites will have the resources in place for any or all of these feedback measures. We will work with each site to determine their capacity.

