### Setting

This study will take place in 10 sites/ambulance Communication Centres distributed in 5 Canadian provinces/regions. They are all associated with sophisticated high-performing paramedic services and receiving hospitals already providing OHCA outcomes data to the CanROC network. Together, these 10 ambulance Communication Centres provide services to an estimated population of 13,919,809 [range 107,406 – 4,800,000], see Table 1. They process more than 1,725,000 9–1-1 calls per year, approximately 8312 of which are for eligible non-traumatic OHCA for which resuscitation is attempted. These sites have also been selected because their ambulance telecommunicators have various training backgrounds, and utilize various types of systems/platforms. All the selected Communication Centres have been providing telecommunication-assisted CPR instructions since or before April, 2004. Our research group has a decade-long history of collaboration with most of these partners. They have all provided a letter in support of this proposed project.

**Table 1 Tab1:** Annual 9–1-1 call volume, with sudden cardiac death distribution, per study site catchment area

Province	Community	Catchment Population	9–1-1 calls/year	Eligible SCD cases/year
British Columbia	Entire Province	4,800,000	600,000	2800
Alberta	Edmonton	4,100,000	600,000	2400
	Calgary			
Ontario	Toronto	2,790,000	280,000	1650
	London	455,526	66,000	291
	Niagara	431,346	60,000	250
	Sudbury	161,531	14,000	134
	Thunder Bay	107,406	9000	102
Nova Scotia	Entire Province	1,000,000	84,000	585
PEI	Entire Province	146,000	12,000	100
	Total	13,991,809	1,725,000	8312

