### Data analysis

#### Overall survival to hospital discharge and community bystander CPR rates – objectives 1 and 2

Individual time series plots for each of the 5 regions will be created to visually inspect the immediate and long-term effects of the intervention, and the presence of trends, cyclical patterns, and outliers. The aggregated monthly rates in each region, expressed as percentages, will be analyzed using a simple linear segmented autoregressive model. To avoid instability due to small numerators and denominators at some sites, multiple sites within the same region will be pooled for the analysis where necessary. The model will include fixed terms for time pre-intervention, intervention, and time post-intervention. The implementation period will be censored from analysis by coding the intervention variable as missing during these months [43]. The model will be estimated using maximum likelihood estimation. Statistical significance will be obtained as the estimated beta coefficients divided by their standard errors with standard errors accounting for the autoregressive parameters. As the primary analysis will be conducted at the aggregate level, no covariates will be adjusted for in this analysis. We will assess serial autocorrelation, non-stationarity, and seasonality using the Durbin-Watson statistic, Dickey-Fuller unit root test, and visual inspection of residual plots against time. The fit of the final model will be assessed by inspecting residuals around the predicted regression lines. In case of substantial non-normality, the analysis will be conducted on the log or logit scale. The effect of the intervention will be expressed for each outcome as intercept and slope changes, where the former can be interpreted as the immediate effect of the intervention and the latter as the gradual effect of the intervention on each outcome over time. We will also evaluate the difference, at 12 months post-implementation, between the fitted post-implementation rates and the projected rates estimated using only the pre-intervention data. This represents the counterfactual effect, that is, the difference between the observed rate and the rate that would have been observed had the intervention not been implemented. We will express these differences on absolute or relative scales, with 95% confidence intervals (CI) calculated using the method of Zhang et al. [44]

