To obtain pooled estimates across all five regions, two methods will be used: First, we will use a random effects meta-analytical approach to pool the five region-specific intervention effect estimates and their standard errors. Next, we will use generalized linear mixed effects regression of the site-specific data with random intercepts for the sites and random slopes for time. All analyses will be conducted using SAS version 9.4 (SAS Institute, Inc., Cary, North Carolina).

#### Successful completion of telecommunication-assisted CPR instructions and frequency of CPR instructions leading to chest compressions in rare victims not in cardiac arrest – objective 3

We will use descriptive statistics with 95% CIs to describe successes in various stages of the implementation of CPR instructions (e.g. instructions offered, provided, completed, chest compressions initiated), and the frequency with which chest compressions are (rarely) going to be provided to a victim not in cardiac arrest.

#### Frequency and impact of agonal breathing on OHCA recognition by telecommunicators – objective 4

The frequency and impact of agonal breathing (proportion of missed OHCA as a result of agonal breathing) will be reported using kappa and descriptive statistics with 95% CI. Sensitivity, specificity, negative and positive predictive values will be computed with 95% CIs for the ability of ambulance telecommunicators to recognize OHCA over the telephone. OHCA recognition rates will be compared in the before and after periods using statistical analyses described above for Objectives 1 and 2.

#### Speed with which OHCA is recognized and telecommunication-assisted CPR instructions are initiated – objective 5

Descriptive statistics with 95% CIs will be used to describe various time delays occurring during telecommunication-assisted CPR instructions (e.g. time to OHCA recognition, to initiation, and to completion of instructions). We will compare these time intervals (continuous variable) in the before and after periods using statistical analyses similar to those described above for Objectives 1 and 2.

#### Objectives 6, 7, and 8

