In addition to the meta-analytic (across all sites) approach proposed for the analyses of Objectives 1 and 2, we plan to stratify our interrupted time series analyses to explore the impact of 6) the studied community/site; 7) the telecommunication system/platform used; and 8) the telecommunicators’ training background and current local training on agonal breathing on the previously stated primary and secondary outcomes (Objectives 1–5).

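### The mixed model used as the second pooling method has no random intervention effect, so its standard error for the level change is too small if sites respond differently

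*Protocol article*

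**What the plan says.** The Study design section gives three reasons for the interrupted time series. The third is: "It will account for heterogeneity across sites in their underlying baseline trends and changes in response to the intervention".

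The Data analysis section fits a segmented model in each region: "The model will include fixed terms for time pre-intervention, intervention, and time post-intervention". The result is reported in the form "The effect of the intervention will be expressed for each outcome as intercept and slope changes", together with the difference from the projected rate at 12 months.

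Two pooling methods follow.
- "First, we will use a random effects meta-analytical approach to pool the five region-specific intervention effect estimates and their standard errors".
- A "generalized linear mixed effects regression of the site-specific data with random intercepts for the sites and random slopes for time".

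For Objectives 6 to 8 the same section adds: "we plan to stratify our interrupted time series analyses to explore the impact of 6) the studied community/site".

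The Setting section states: "This study will take place in 10 sites/ambulance Communication Centres distributed in 5 Canadian provinces/regions". It adds that sites were chosen partly because their training backgrounds and dispatch systems vary. On the report-card component, the Educational intervention section says: "We understand that not all sites will have the resources in place for any or all of these feedback measures".

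**The concern.** The segmented model treats the intervention as a term separate from time. A random slope for time therefore does not make the level change random. As written, the mixed model lets each site have its own baseline and trend but gives all 10 sites one immediate response.

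The protocol itself has reasons to expect otherwise. Training and platforms differ, the feedback component will not be delivered everywhere, and three objectives ask how site, platform and training alter the outcomes.

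If responses differ and the model has no term for it, that variation is left out of the standard error of the pooled level change. The confidence interval is then too narrow. This matters because the mixed model is the only pooled analysis of site-specific data, and it applies to the primary outcome, survival to discharge.

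**Working it through.** **The plan's own figure.** The Sample size section gives 6,000 to 7,000 cases a year: 6,000/12 = 500 and 7,000/12 = 583 a month, so the stated 500 is reproduced at the lower end. Its 50 survivors in 500 cases imply 10% survival. No power, standard error or between-site SD is stated.

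**Inputs from the protocol.** 10 sites; 12 months before and 12 after; Table 1 volumes (2800, 2400 for Edmonton and Calgary together, 1650, 291, 250, 134, 102, 585 and 100, total 8312); hypothesised gains of 5 points in survival and 10 points in bystander CPR; past bystander CPR of 15–25%.

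**Assumed inputs.** Alberta split 1200/1200; CPR baseline 25%; site SD 0.2 (logit) for the intercept and 0.1 per year for the time slope; between-site SD of the level change, tau, at 0, 25%, 50% and 100% of the hypothesised effect.

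**Effects on the logit scale.**
- Survival 10% to 15%: ln(0.15/0.85) − ln(0.10/0.90) = 0.46, so tau = 0, 0.116, 0.231, 0.463.
- CPR 25% to 35%: ln(0.35/0.65) − ln(0.25/0.75) = 0.48, so tau = 0, 0.12, 0.24, 0.48.

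**Simulation.** 250 replicates per setting, REML, normal approximation on the logit scale with known sampling variance. Results for the model as stated:

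| Outcome | tau, % of effect | Level change: SE/true SD | 95% CI coverage | 12-month difference: SE/true SD |
|---|---|---|---|---|
| Survival | 0 | 1.01 | 94% | 0.96 |
| | 25 | 0.82 | 92% | 0.91 |
| | 50 | 0.73 | 88% | 0.90 |
| | 100 | 0.43 | 61% | 0.71 |
| CPR | 0 | 0.93 | 92% | 0.98 |
| | 25 | 0.83 | 91% | 0.91 |
| | 50 | 0.55 | 73% | 0.80 |
| | 100 | 0.31 | 44% | 0.52 |

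The mean SE of the level change stays at about 0.102 (survival) and 0.073 (CPR) whatever tau is. The random time slope does not absorb the differing responses.

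**Check by hand.** If sites are weighted roughly by cases, heterogeneity adds tau × √(Σn²)/Σn to the true SD, in quadrature. Σn² = 13,970,266 and Σn = 8312, so the factor is 3737.7/8312 = 0.45.
- Survival, tau 0.231: √(0.102² + 0.104²) = 0.146; ratio 0.102/0.146 = 0.70 (simulated 0.73).
- CPR, tau 0.24: √(0.073² + 0.108²) = 0.130; ratio 0.073/0.130 = 0.56 (simulated 0.55).
- Survival, tau 0.116: √(0.102² + 0.052²) = 0.1145; ratio 0.89 (simulated 0.82).

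The last gap is within simulation error: an SD from 250 replicates has a relative error of about 1/√500 = 4.5%. The 0.93 for CPR at tau = 0 is likewise not evidence of a fault.

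**Second simulation, percentage scale.** 1,000 replicates, survival 8%, true mean effect 0, site SDs again assumed. With tau = 2 points, the mean SE is 0.91 against a true SD of 1.29, and type I error is 17%; at 3 points it is 30%. Scaling down to 1 point: (1.29² − 0.91²)/4 = 0.209, so the true SD is √(0.828 + 0.209) = 1.02. The critical ratio becomes 1.96 × 0.91/1.02 = 1.75, a type I error of about 8%.

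**With a random level change added (logit simulation).** The level-change ratio is 0.88–1.03 and coverage 91–95% over the whole range. For the 12-month difference they are 0.94–1.00 and 92–96%.

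**The case against.** The strongest reply is that the design rationale describes the plan as a whole, not this one model, and that the plan deals with heterogeneity elsewhere: separate regional models, a random-effects meta-analysis named first, and stratified analyses by site, platform and training. This stands in part. A reader might infer that the plan ignores differing responses; it does not. But the meta-analysis pools five regions, and in Table 1 Ontario contains five sites and Alberta two, so differences within those regions are not carried. The stratified analyses are exploratory and do not correct a pooled standard error.

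A second reply is that a journal article condenses, and the full random-effects structure belongs in an analysis plan not shown here. That would answer a complaint of missing detail. Here the random terms are listed, and the list leaves one out. If the time slopes are meant to include post-intervention time, slope change would vary by site, but the level change would still be common.

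A third reply is that the harm depends on an SD the documents do not give. This stands. A reader might infer that the pooled interval is too narrow in any case. With tau = 0 there is essentially no understatement, and at 25% of the effect coverage is still 91–92%.

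A reader might also infer that the two pooled results will disagree. They may, but this was not computed.

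Finally, neither simulation fits the planned generalized linear model to sparse counts. Prince Edward Island (100 cases a year) and Thunder Bay (102) have about 8 cases a month, under one survivor at 10%. Convergence with a third random effect is not assured.

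**Conclusion.** The point holds for the second pooling method only. As written, that model imposes one level change on all sites, against the stated rationale and the protocol's own account of how sites differ. How much this matters depends on an unknown between-site SD: essentially nothing at zero, an SE about a fifth too small at 25% of the hypothesised effect (less for survival by the hand check), and 27% (survival) to 45% (CPR) too small at 50%. For the 12-month difference at 50%, the shortfall is 10% and 20%. These sizes rest on the assumed site SDs, the equal Alberta split and Table 1 volumes. With the lower case numbers in the Sample size section, sampling error would be larger and the relative shortfall somewhat smaller.

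The protocol does not say which pooled estimate prevails if the two differ, so the narrower interval could become the headline. This should be fixed before analysis. It does not invalidate the plan, because the method named first allows for heterogeneity between regions.

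**What to change.** In the mixed model, add a random site effect for the intervention term (level change), and for the slope change if it can be estimated. Use small-sample degrees of freedom based on the 10 sites, and report the between-site SD of the effect with the pooled estimate. State in advance that, if this model does not converge, the random-effects meta-analysis is the pooled analysis of record.

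The small-sample correction matters. In the percentage-scale simulation, the added term alone brought type I error to 6–7% with a normal reference, and to 3–4% with t on 9 degrees of freedom.

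The cost is small. If sites respond alike, the SE rises from 0.91 to 0.94 points on the percentage scale, and on the logit scale from 0.102 to 0.107 (survival) and 0.073 to 0.076 (CPR). The remaining cost is some convergence risk from the smallest sites, which the named fallback covers.

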**Pilot Evaluation of Telecommunication-Assisted CPR Instructions in Ottawa**

This before-after study took place over an 18-month period before and after the introduction of telecommunicator-assisted CPR instructions in the Communication Centre in Ottawa, Ontario. A total of 529 cases were included and bystander CPR rates increased from 16.7 to 26.4% (95% confidence interval (CI) 8.5–11.3%; p-0.006) [8].
2)**Multi-Centre Evaluation of Effectiveness of Telecommunication-Assisted CPR Instructions**

This study took place in several Ontario Communication Centres. In this before-after interrupted time series study including 6494 cases before and after the introduction of telecommunicator-assisted CPR instructions, bystander CPR rates increased from 14.9 to 28.7% (*p* < 0.0001) and survival increased from 4.1 to 5.2% (adjusted odds ratio 1.28; 95% CI 1.02–1.62; *p* = 0.04). Telecommunicators recognized 65.9% of all OHCA. Agonal breathing (present in 22.7% of all OHCA) accounted for 47.6% of missed diagnoses, resulting in inappropriately withheld bystander CPR for 240 victims [11, 12].
3)**Systematic Reviews of Factors Leading to the Recognition of Cardiac Arrest by Telecommunicators**

These two systematic literature reviews were peer-reviewed by the International Liaison Committee on Resuscitation (ILCOR) and provided the scientific background from which the 2010 and 2015 resuscitation guidelines for telecommunication-assisted CPR instructions were derived [13, 14]. The reviews conclude that telecommunicators should receive specific instructions on how to recognize the presence of agonal breathing in order to improve their recognition of cardiac arrest.
4)**National Survey of Factors Associated with the Successful Recognition of Agonal Breathing**

This National Survey was distributed to telecommunicators from 24 cities in four provinces (*n* = 404). The survey was developed using the constructs of the Theory of Planned Behavior, which elicits salient attitudes, social influences and control beliefs suggesting corresponding educational behavior-change techniques to improve recognition of agonal breathing and cardiac arrest [15, 16].
5)**Before-After Controlled Pilot Study**

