In this recently-completed study we demonstrated we could improve absolute bystander CPR rates by 12.9% and survival to hospital discharge by 8.4% in Ottawa after implementing a theory-based (TPB) educational program on agonal breathing for telecommunicators. Agonal breathing was present in as many as 25.6% of cases, but was responsible for only 15.8% of missed cases (compared to almost 50% previously) [7].
6)**National Survey of Canadian Communication Centres**

Finally, most recently, a National Survey of all Canadian Communication Centres was undertaken to obtain information on their organizational structure, dispatch systems in use, education curriculum and performance monitoring. The information obtained indicates that most centres utilize the Medical Priority Dispatch System, require a High School diploma as minimum entry level education and telecommunicators receive no or minimal education in recognizing agonal breathing as a sign of OHCA [17].

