#### Hypothesis

We hypothesize that the educational program will increase absolute OHCA recognition and bystander CPR rates by at least 10%, and absolute OHCA survival by 5% or more.

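### Objective 4's named measure of agonal-breathing impact is a share of missed arrests, which does not by itself show whether recognition of agonal cases improved

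*Protocol article*

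**What the plan says.** In the protocol article, Objectives, the fourth objective is to quantify how often agonal breathing occurs and how it affects recognition of OHCA after the programme. Data analysis, objective 4, then fixes the measure: the "impact of agonal breathing (proportion of missed OHCA as a result of agonal breathing". It is reported descriptively with a 95% CI. The same paragraph plans the frequency of agonal breathing, the sensitivity, specificity and predictive values of telecommunicator recognition, and a before-after comparison of recognition rates with the time-series methods of objectives 1 and 2. None of these is split by agonal status.

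The article uses the same share for its earlier work. For the multi-centre study (Prior related work, item 2) it reports "Telecommunicators recognized 65.9% of all OHCA" and "Agonal breathing (present in 22.7% of all OHCA) accounted for 47.6% of missed diagnoses". For the Ottawa pilot of this programme (item 5) agonal breathing was "responsible for only 15.8% of missed cases (compared to almost 50% previously".

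The Hypothesis section concerns recognition overall: "the educational program will increase absolute OHCA recognition and bystander CPR rates by at least 10" per cent.

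**The concern.** Numerator and denominator of the share are both counts of misses, and the programme may reduce both. Under Educational intervention, the video covers early signs of cardiac arrest in general, with agonal breathing as one of them. Report cards are foreseen for cardiac arrest calls of any kind, as far as each site has the capacity. The share therefore responds to the relative change in agonal and non-agonal misses, not to recognition of agonal cases as such.

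The intervention is built on the idea that telecommunicators fail to recognise arrest when agonal breathing is present. If training helped with all causes of missed arrest, the share could look as though nothing had changed for agonal cases. If it helped only with other causes, the share would rise as though agonal cases had become harder to recognise.

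**Working it through.** **Inputs** (Prior related work, item 2): overall recognition R = 65.9%; agonal frequency f = 22.7%; share of misses attributed to agonal breathing s = 47.6%.

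**Assumption:** misses attributed to agonal breathing are the misses among agonal cases.

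**Starting position**
- All misses: 1 − 0.659 = 0.341 of OHCA.
- Agonal misses: 0.476 × 0.341 = 0.162. Other misses: 0.524 × 0.341 = 0.179.
- Recognition in agonal cases: 1 − 0.1623/0.227 = 28.5%.
- Recognition in other cases: 1 − 0.1787/0.773 = 76.9%.
- Check: 0.1623/(0.1623 + 0.1787) = 47.6%, the article's figure.

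**How the share moves.** Let a and b be the fractions of agonal and other misses that remain after training.
- Share = 0.1623a/(0.1623a + 0.1787b), which depends only on the ratio a/b.
- Agonal recognition = 1 − 0.715a, where 0.715 = 0.1623/0.227. It depends only on a.

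| Scenario | a | b | Agonal recognition | Overall recognition | Share of misses |
|---|---|---|---|---|---|
| Before | 1 | 1 | 28.5% | 65.9% | 47.6% |
| Only agonal misses halve | 0.5 | 1 | 64% | 74% | 31% |
| Both halve | 0.5 | 0.5 | 64% | 83% | 47.6% |
| Agonal halve, others fall to a quarter | 0.5 | 0.25 | 64% | 87% | 64.5% |
| Agonal unchanged, others halve | 1 | 0.5 | 28.5% | 75% | 64.5% |

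The last two rows give the same share, although agonal recognition more than doubles in one and does not change in the other.

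**Size of gain needed for a flat share.** Suppose agonal recognition doubles to 57.0%, so that agonal misses fall by 39.8%.
- Other recognition unchanged: share 35.3%.
- Overall recognition up by exactly 10 points (other recognition 81.5%): share 40.5%.
- Other misses also down 39.8% (other recognition 86.1%, overall 79.5%, a gain of 13.6 points): share flat at 47.6%.
- Other recognition 90% (overall 82.5%): share 55.8%.

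The share can also fall without any gain: with agonal recognition fixed at 28.5% and other recognition worsening to 70%, it drops to 41.2%.

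**Other inputs.** With the rounded figures under Importance of this research (about 25% agonal, up to 50% of misses) and the same R, starting agonal recognition is 31.8%. If it doubles, the share is flat at an overall recognition of 81.8%.

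**Back-calculation.** Agonal recognition = 1 − share × (1 − R)/f. With share 55.8%, R 82.5% and f 22.7%: 1 − 0.558 × 0.175/0.227 = 57.0%, the value put in. The planned quantities therefore recover it under the stated assumption.

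**Pilot.** The article does not state the pilot's overall recognition. With 25.6% agonal and a 15.8% share, assumed overall recognition of 60% to 90% gives agonal recognition from 1 − 0.158 × 0.40/0.256 = 75% to 1 − 0.158 × 0.10/0.256 = 94%.

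**The case against.** A reader might infer that objective 4 cannot show whether training helped agonal cases, or that the trial's mechanism will be judged on this ratio. The documents support neither reading. The share is descriptive, with no test or success criterion attached, and the Hypothesis section concerns overall recognition, bystander CPR and survival. Frequency, share and overall recognition will all be reported, and together they allow the back-calculation above. In the fourth scenario a careful reader could see agonal misses fall from 16% to 8% of OHCA. Agonal status is also coded on each reviewed call.

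Nor do the documents predict that the share will stay flat or rise. That needs other misses to fall at least in proportion. The flat and rising scenarios in the table need overall gains of about 17 and 21 points, the latter with other recognition near 94% (1 − 0.045/0.773). Such gains fit a hypothesis of at least 10 points, but no section forecasts so large an effect on non-agonal cases. The rehearsal module uses agonal-breathing cases, and the article allows that some sites may lack resources for feedback. In the pilot the share moved as intended, and the implied 75% to 94% is well above 28.5%, so the pilot figure is no evidence against the programme.

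Finally, a split by a coded variable is often left to an analysis plan. That holds for tabulation detail. Here, however, the article itself names the impact measure, and that measure does not match the stated objective. The back-calculation is not planned, brings no interval or before-after comparison of its own, and is only approximate if the attribution of a miss to agonal breathing differs from its mere presence. The article has reviewers record reasons for non-recognition, so the two may differ.

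**Conclusion.** The point holds in a limited form. The measure named for objective 4 describes the composition of missed arrests and does not by itself show whether recognition improved when agonal breathing was present. With the article's own figures, a share of 47.6% is compatible with agonal recognition of 28% or 64%, and so is a share of 64.5%. The share falls as intended only if agonal misses fall proportionally more than others. The only before-after comparison specified for objective 4 is overall recognition.

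The numbers rest on the prior multi-centre study as the starting position and on equating attributed misses with misses in agonal cases. The behaviour of the ratio does not depend on those particular values. This is a secondary objective and the data needed are already collected. The weakness lies in which measure is named and compared.

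**What to change.** Under Data analysis, objective 4, add two measures, each compared before and after:
- recognition among eligible OHCA with agonal breathing and among those without;
- missed arrests with agonal breathing as a percentage of all eligible OHCA.

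Use the objective 1 and 2 model where monthly counts allow. Elsewhere use pooled data or a patient-level model with a period-by-agonal term. Prince Edward Island, a region of its own, has 100 eligible cases a year (Table 1): 100/12 ≈ 8 a month, and 8.3 × 0.227 ≈ 2 agonal cases, too few for a regional monthly series. Keep the share as a descriptive figure for comparison with the earlier studies.

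State as a limitation that agonal status is coded from what the caller describes. Training may change how often callers are asked about breathing, and so the recorded status. This affects both new measures, so neither is free of the problem.

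The cost is some extra analysis and limited precision in small regions. No new data collection is needed, because agonal status and recognition are already extracted from the recordings of eligible and missed calls.
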